#### Interim analyses {21b}

To review results and serious adverse effect in the intervention arm, an independent data and safety analysis will be performed after recruitment of 100 patients. A conservative approach using a significance level of less than 0.001 in the comparison between groups will be used before making any recommendation to terminate the trial prematurely. The adequacy of the power calculation will also be assessed at this time and preliminary data used to inform decision on the need to extend patient recruitment.

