### Trial design {8}

The SWEMMA trial is designed as a randomized, controlled, open, national, multicenter superiority trial with two parallel groups and a primary endpoint of reoperation within 3 months following either procedure. Clinical secondary outcomes assessments at 3 months and 12 months will be blinded. Randomization will be performed in blocks with 1:1 allocation.

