#### Sample size {14}

The study will include at least 288 patients (control + intervention), with 144 patients per arm. The required total sample size was estimated based on the expected proportion of re-operations (primary outcome) within the control and intervention arms using a two-sided likelihood ratio test with alpha = 0.05 (type I error), beta = 0.2 (type II error), and power of 80% (1-beta). The null hypothesis for this study is that there is no difference between embolization versus surgery for cSDH. The alternative hypothesis was conservatively pre-specified as a different proportion of re-operations between the groups (i.e., a two-sided test was used for power calculation). The expected proportion in the control arm was defined as 17%. This number was based on the average excess operations per patient operated for cSDH in South of Sweden (Skåne) during the last 5 years (2016–2020), as well as a report from the Skåne University Hospital [17]. The expected proportion in the intervention arm was set to 6.5% based on previous reporting evaluating the safety and efficacy of embolization of cSDH as sole treatment [13].

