### Statistical methods

#### Statistical methods for primary and secondary outcomes {20a}

All statistical analyses will be performed using SPSS (Armonk, NY: IBM Corp). All performed statistical tests will be two-sided and the statistical significance level set at *p* < 0.05. Baseline characteristics between intervention and control group will be assessed using mean (standard deviation, SD) and median (interquartile range, IQR) for continuous variables and frequency (percent, %) for categorical variables. Differences across groups will be tested using two-sided Student’s *t*-test and Mann–Whitney test for continuous data and the chi-square test for categorical data.

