#### Data Safety Monitoring Board

The Data Safety Monitoring Board (DSMB) comprises at least 3 non-Investigator clinicians with expertise in interventional neuroradiology/neurosurgery that will review all adverse events occurring in the study according to the DSMB Charter. The DSMB will meet and review all clinical events continuously.

Any event meeting the definition of serious adverse event (SAE) must be adjudicated by the DSMB. The DSMB will also be provided with listings of all events and may choose to adjudicate events that are not serious in nature. Members may discuss any event with the investigator who was involved with the subject in question. The DSMB will use the same rating scale for relatedness. The DSMB adjudicated adverse events will be used in the analysis of the primary safety endpoint; DSMB will review and adjudicate the Medical Monitor’s categorization of event type and severity using the rating system previously referenced.

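### The interim rule sets one threshold, p < 0.001, before any recommendation to terminate and does not exempt harm, which the same look is meant to review

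*Protocol article*

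**What the plan says.** Protocol article, Interim analyses {21b}, gives the purpose and timing of the look in one sentence: "To review results and serious adverse effect in the intervention arm, an independent data and safety analysis will be performed after recruitment of 100 patients". The next sentence gives the decision rule: "a significance level of less than 0.001 in the comparison between groups will be used before making any recommendation to terminate the trial prematurely". It names no outcome and no test, and it does not separate benefit from harm.

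The section Data Safety Monitoring Board adds a second layer of oversight: "The DSMB will meet and review all clinical events continuously". That review follows a DSMB Charter, which is not shown. The section covers review and adjudication of events. It states no criterion for recommending termination and does not refer to the interim threshold.

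Two other statements fix the setting for the arithmetic: "Randomization will be performed in blocks with 1:1 allocation" (Trial design {8}) and "All performed statistical tests will be two-sided" (Statistical methods {20a}).

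**The concern.** A very strict interim level is a sound guard against claiming benefit too early. The protocol's wording extends it to every reason for terminating. Since the sentence just before it names serious adverse effects, the plain reading is that a recommendation based on harm at this look faces the same barrier.

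The two errors are not alike. Stopping early for apparent benefit can create a false superiority claim. Stopping for harm cannot, so the strict level is not needed there to protect the primary test. Its cost falls on safety: with about 50 patients per arm, a marked excess of uncommon serious events on embolization would often fall short of p < 0.001. A board that follows this section to the letter would then have no basis in it for a recommendation to terminate.

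**Working it through.** **Inputs from the protocol.** Look "after recruitment of 100 patients", allocation 1:1, so about 50 v 50; two-sided tests; threshold p < 0.001. No test is named for the look, so three are shown: Fisher exact, Pearson chi-square, and the likelihood ratio test that the protocol uses for its sample size. No expected serious-event rate is given for either arm, so every rate in step 3 is an assumption.

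**Step 1: the plan's own figure.** The protocol gives no operating characteristics for the look, but its sample size can be checked. For 17% v 6.5% (mean 11.75%), the likelihood ratio formula is n per arm = (1.960 + 0.842)² / {2[K(0.17) + K(0.065)]}, where K(p) = p ln(p/0.1175) + (1−p) ln((1−p)/0.8825). K(0.17) = 0.01189 and K(0.065) = 0.01555, so n = 7.849 / 0.05487 = 143.1, which rounds up to the stated 144. The sample size is not at issue.

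**Step 2: events needed for p < 0.001 at 50 v 50.**

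| Control events | Fisher | Pearson | Likelihood ratio |
|---|---|---|---|
| 0 | 11 | 10 | 8 |
| 1 | 13 | 13 | 11 |
| 2 | 15 | 15 | 14 |
| 5 | 20 | 20 | 19 |

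Examples with 0 control events:
- Pearson, 10 v 0: z = 0.20 / √(0.10 × 0.90 × 2/50) = 0.20/0.06 = 3.33, p = 0.0009, which meets the rule.
- Fisher, 10 v 0: p = 0.0012, which does not. 11 v 0 gives p = 0.0005.
- Likelihood ratio, 8 v 0: 2[8 ln(0.16/0.08) + 42 ln(0.84/0.92) + 50 ln(1/0.92)] = 11.8, p = 0.0006, which meets the rule. 7 v 0 gives p = 0.0014.

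Observed fourfold splits of 4 v 1, 8 v 2, 12 v 3 and 16 v 4 give Fisher p = 0.36, 0.092, 0.023 and 0.0050. The first to pass is 20 v 5 (p = 0.00097).

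**Step 3: chance of meeting the rule.** For true rates pT (embolization) and pC (control), sum Bin(i; 50, pT) × Bin(j; 50, pC) over all pairs with i > j and two-sided p < 0.001.

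| Assumed rates, embolization v control | Fisher | Pearson | Likelihood ratio |
|---|---|---|---|
| 10% v 2% | 0.4% | 0.9% | 5% |
| 20% v 5% (fourfold) | 9% | 10% | 18% |
| 32% v 8% (fourfold) | 33% | 38% | 42% |
| 40% v 10% (fourfold) | 53% | 59% | 62% |
| 50% v 12.5% (fourfold) | 76% | 82% | 83% |
| 68% v 17% (fourfold) | 97% | 98% | 99% |
| 30% v 10% | 16% | 20% | 22% |
| 34% v 17% | 6% | 8% | 9% |

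For a fourfold excess the chance passes 50% at a control rate of 9.7% (Fisher), 9.1% (Pearson) or 8.8% (likelihood ratio).

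**Step 4: completeness of data.** The look is triggered by recruitment, not by completed follow-up. If the assumed rates are read as rates over full follow-up, fewer events will have been seen at the look and the chances are lower than tabulated.

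**The case against.** The best counter-argument is that the threshold governs one scheduled analysis only. The DSMB reviews all clinical events continuously under its own Charter, and nothing applies p < 0.001 to that review. Harm guidelines commonly sit in such a Charter, and a journal article need not repeat them. Deaths must also be reported to the Ethics Committee and Competent Authority, and the protocol allows changes without prior approval to remove immediate hazards. This stands as mitigation. A reader might infer that the board is barred from ever recommending termination for harm, or that the safety look is disabled. The documents do not support that. Nor does the mitigation dispose of the point: the article states a rule covering any termination recommendation, and a Charter with a lower bar for harm would conflict with it.

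A reader might also infer that a fourfold excess of serious events would generally miss the threshold. That depends on a control rate the protocol does not give. The serious adverse event definition is broad and includes in-patient hospitalization, and 17% of controls are expected to be reoperated. If reoperations count as serious events, the control rate could exceed 10%, and a fourfold excess would then usually meet the rule.

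It would also be too strong to say that the strict level does nothing when applied to harm. It lowers the chance of abandoning the trial on a chance imbalance among many event types.

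Finally, the purpose clause, "To review results and serious adverse effect in the intervention arm", might suggest that only one arm is examined. The rule itself compares the groups, and the DSMB receives listings of all events, so this is a matter of wording.

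**Conclusion.** The point holds as a defect in a stated rule. The interim section makes p < 0.001 a condition for any recommendation to terminate, names serious adverse effects as a purpose of the same look, and is not qualified elsewhere in the article.

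Its size depends on unknown event rates. The rule is hard to meet for uncommon serious events: at most 18% under any of the three tests for 20% v 5%, and at most 5% for 10% v 2%. It is also hard to meet for smaller relative excesses of common events: at most 22% for 30% v 10% and 9% for 34% v 17%. It is not hard to meet for a fourfold excess once the control rate is above about 10%.

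These figures assume 50 v 50, independent binary events and the assumed rates shown. The practical consequence is softened by continuous DSMB review under a Charter not shown. Severity: should be fixed.

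**What to change.** In Interim analyses {21b}, state that p < 0.001 on the primary outcome applies only to a recommendation to stop for benefit. Add that a recommendation on grounds of harm is not subject to this threshold and rests on DSMB review of deaths and serious adverse events in both arms, under the DSMB Charter. Bring that section and the Data Safety Monitoring Board section into agreement, and check that the Charter says the same. Make the change before the look is carried out.

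The cost is a sentence or two in the protocol, with matching text in the Charter, and no extra patients. The type I error for superiority is not increased, because stopping for harm cannot yield a superiority claim. The small downside is a somewhat higher chance of stopping on a chance safety imbalance.

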#### Plans to promote participant retention and complete follow-up {18b}

The study participants are recommended to follow the study protocol. Included participants refusing allocated treatment and crossovers will remain in the study and be included in the intention-to-treat analysis. Additional participants may be enrolled to allow the study to meet its designed sample size dimensions to allow for a sufficiently powered per-protocol-analysis.

Participation in this investigation is voluntary, and the subject may withdraw at any time. All enrolled subjects will be included in data analysis unless they withdraw permission for their data to be used. The sponsor will retain and continue to use any data collected prior to the withdrawal of consent, unless specified by the subject.

In the event the subject chooses to withdraw, he/she will be instructed to contact the Investigator immediately. Withdrawal from the investigation will not affect the subject's standard of care. The subject will be informed of any significant information regarding new findings that may develop during the course of the study that may relate to his or her willingness to continue participation as a study subject.

Subjects will participate in their routine follow-up and allow this data to be gathered. If their participation is terminated, any of their data which has been already gathered will continue to be included. The completion of a subject’s participation in the study or early departure from the study must be fully documented in the subject’s medical records. Subjects will be considered discontinued from the study if any of the following occur:Subject voluntarily withdraws from the study: A subject may withdraw consent from study participation at any time. The subject will be offered to give a reason for their withdrawal. If voluntarily given, this reason will be recorded in the eCRF.Subject withdrawn from the study by the investigator: An investigator may withdraw an enrolled subject from the study for the following reason:

If participation in the study is life threatening for the subject or at the investigators own discretion.

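### The interim p < 0.001 condition is worded to cover every recommendation to stop, so it binds stopping for harm as well as for benefit; limit it to benefit and reconcile it with the DSMB section

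*Protocol article*

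**What the plan says.** Protocol article, Interim analyses {21b}, gives the purpose of the look as "To review results and serious adverse effect in the intervention arm" and its timing as "an independent data and safety analysis will be performed after recruitment of 100 patients". It then sets one condition: a "significance level of less than 0.001 in the comparison between groups will be used before making any recommendation to terminate the trial prematurely". It does not name the endpoint, the test or the direction of effect. At the same look the power calculation is reassessed, with "preliminary data used to inform decision on the need to extend patient recruitment". No rule is given for that decision, and the text does not say whether pooled or by-arm data are used.

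The Data Safety Monitoring Board section sets up a board of non-investigator clinicians who review events continuously under a charter and adjudicate every serious adverse event. It gives no criterion for recommending that the trial stop, and it does not refer to the 0.001 condition.

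**The concern.** A very strict interim threshold is a sound way to guard against stopping too early for benefit, because it leaves almost all of the 5% error for the final analysis. Harm is a different case: a monitoring board should be able to act on a worrying imbalance well before it is proven to that standard. Here the one stated threshold is attached to any recommendation to terminate, in a paragraph that opens with serious adverse effects. Read as written, a clinically serious excess of events in the embolization arm could not support a recommendation to stop unless it reached p < 0.001 with about 50 patients per arm. What is at stake is the protection of participants.

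**Working it through.** **Inputs.** The look is at 100 recruited patients with p < 0.001 (Interim analyses {21b}). Allocation: "Randomization will be performed in blocks with 1:1 allocation" (Trial design {8}), so about 50 per arm. For sidedness, Statistical methods {20a} says "All performed statistical tests will be two-sided and the statistical significance level set at" p < 0.05, so 0.001 is taken as two-sided, with critical value z = 3.291. The planned reoperation rates are 17% and 6.5%, with 144 per arm (Sample size {14}). No serious adverse event rates are given, so the harm scenarios are assumptions shown over a range.

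**The plan's own figure.** For the likelihood ratio test, n per arm = λ / g. Here λ = 7.849 (two-sided 0.05, 80% power), g = 2[H(0.17) + H(0.065) − 2H(0.1175)] and H(p) = p ln p + (1 − p) ln(1 − p). This gives g = 2(−0.45589 − 0.24051 + 0.72383) = 0.05487 and n = 143.06, rounded up to 144. The planned 288 is reproduced.

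**Cost of the threshold as an efficacy boundary.** One look at 0.001 with 0.05 kept at the end gives an overall error of 1 − P(|Z₁| < 3.291, |Z₂| < 1.960), with correlation √(100/288) = 0.589. The result is 0.0504, so for benefit the threshold is harmless.

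**Events needed to cross for harm, 50 per arm.** The interim section names no test, so three are shown.

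| Control events | Fisher | Pearson | Likelihood ratio |
|---|---|---|---|
| 0 | 11 | 10 | 8 |
| 2 | 15 | 15 | 14 |
| 5 | 20 | 20 | 19 |
| 9 | 26 | 25 | 25 |

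Pearson check: for 20 vs 5, z = (0.40 − 0.10) / √(0.25 × 0.75 × 2/50) = 0.30/0.0866 = 3.46, which crosses. For 19 vs 5, z = 0.28/√(0.24 × 0.76 × 2/50) = 3.28, which just fails.

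**Chance of crossing in the harm direction.** This is the exact sum of binomial probabilities over all tables with p < 0.001 and more events in the embolization arm.

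| Assumed risk, control vs embolization | Fisher | Pearson | Likelihood ratio |
|---|---|---|---|
| 5% vs 10% | 0.1% | 0.2% | 1.1% |
| 5% vs 15% | 1.7% | 2.4% | 6.5% |
| 10% vs 20% | 1.5% | 1.9% | 3.1% |
| 17% vs 34% | 6.0% | 8.1% | 9.2% |
| 10% vs 30% | 16.0% | 19.6% | 22.0% |
| 5% vs 30% | 46.8% | 50.7% | 57.3% |
| 10% vs 40% | 53.1% | 59.0% | 61.8% |

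Normal-approximation check for 10% vs 30%: (0.20 − 3.291 × 0.0800)/0.0775 = −0.82, and Φ(−0.82) ≈ 0.21, in line with the exact values.

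The small sample explains part of this. Even at two-sided 0.05 (Fisher to Pearson), the chances would be 20–30% for 10% vs 20% and 64–73% for 10% vs 30%. The threshold does the rest.

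**Follow-up at the look.** The trigger is recruitment, while the primary outcome takes 3 months. If 288 patients accrue evenly over about 36 months (Trial status), that is 8 per month. About 3 × 8 = 24 of the 100 would then lack the 3-month outcome, leaving about 76 for a reoperation comparison.

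**The case against.** The strongest reply is that this look is not the trial's only safeguard. The DSMB reviews events continuously under its own charter, and guidance on stopping for harm commonly sits in such a charter, which a journal article need not reproduce. This stands in part. A reader might infer that the safety review can almost never act, and the documents do not support that: oversight runs outside this look, and even under the threshold very large harm crosses about half the time. Nor is it right that a tripling could never cross, since 10% vs 30% does so 16–22% of the time. But the charter does not cure the wording. If it lets the board recommend stopping on judgement, it conflicts with a protocol sentence that covers every such recommendation.

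A reader might also infer that the look sets the sample size from unblinded results and inflates type I error. The text says only that preliminary data inform the decision. The comparison between groups needs by-arm data, but nothing says that the power reassessment uses them. Without an extension rule, no inflation can be calculated.

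Nor does the separate provision that "Additional participants may be enrolled to allow the study to meet its designed sample size dimensions to allow for a sufficiently powered per-protocol-analysis" (Plans to promote participant retention {18b}) describe adding patients after a non-significant result. It follows a sentence on refusals and crossovers and refers to the designed sample size, so it is no evidence of an error-control problem.

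Finally, triggering a safety look on recruitment is defensible, especially for procedural events. Waiting for complete 3-month data would delay it.

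**Conclusion.** The point holds as a badly fixed rule: the stated threshold applies to stopping for harm, and nothing in the article lifts it. At about 50 per arm, a doubling of risk from a base of 5% to 17% would meet it less than 10% of the time, and a tripling from 10% to 30% about one time in five. These figures assume the stated risks, full event ascertainment in 50 patients per arm and a two-sided test; the ranges reflect the unnamed test. The threshold is appropriate for benefit. The lack of a stated data basis for extending recruitment is a secondary point of clarity, with no error figure attached.

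**What to change.** In Interim analyses {21b}, state that p < 0.001 applies only to a recommendation to stop for benefit, and that a DSMB recommendation on safety grounds is not conditional on it. Bring the Data Safety Monitoring Board section and the charter into line with that sentence. Keep the look triggered by recruitment, and note that some of the 100 patients will not yet have the 3-month outcome, so the reoperation comparison rests on fewer patients than the safety review.

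Secondarily, state that any decision to extend recruitment uses only the pooled, arm-blind event rate.

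The cost is a wording amendment to the protocol and a check of the charter. The sample size, the timing of the look and the final significance level stay as they are.

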#### Adjustment of significance levels and confidence intervals

The study includes one primary outcome and five secondary outcomes. Threshold for statistical significance is set at *P* < 0.05 for the primary outcome. For secondary outcomes, correction for multiple testing will be performed using a significance level of *p* < 0.01.

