### Oversight and monitoring

#### Composition of the coordinating center and trial steering committee {5d}

Principal investigator.

Trial planning.

Design and conduct of SWEMMA.

Preparation of protocol and revisions.

Preparation of CRFs.

Organizing TMSC meetings.

Publication of study reports.

Member of Steering Committee.

Trial Management and Steering Committee (TMSC).

(see title page for members).

Trial planning.

Agreement on final protocol.

Organization of TMSC meetings.

All TMSC members will be lead- or sub investigators.

Recruitment of subjects and liaising with coordinating site principal investigator.

Reviewing progress of the trial and if necessary, implementing changes to the protocol to facilitate smooth continuation of the trial.

Advice for lead investigators.

Budget administration.

Agreement on final study report publication.

Data management committee.

Independent of the study organizers.

Management of trial IT systems and data entry.

Responsible for CRF functionality and maintenance.

Responsible for trial master file.

Randomization.

Data verification.

Responsible for performing primary outcome analysis.

Lead investigators.

In each participating center, a lead investigator will be identified (senior neurosurgeon/neurointerventionalist), to be responsible for screening, recruitment, data collection, and completion of relevant CRF entries. Lead investigators will be steering committee members.

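### The interim look may extend recruitment on outcome data without limiting them to pooled rates or capping the size, while the final test stays at an unadjusted 0.05, so the stated 5% type I error is not guaranteed

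*Protocol article*

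**What the plan says.** All references are to the protocol article.

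- **Interim analyses {21b}.** An independent data and safety analysis takes place after 100 patients are recruited. It compares the groups, and p below 0.001 is needed before early termination is recommended. At the same time the adequacy of the power calculation is assessed, with "preliminary data used to inform decision on the need to extend patient recruitment".
- **Sample size {14}.** "The study will include at least 288 patients (control + intervention), with 144 patients per arm". On the basis: "The required total sample size was estimated based on the expected proportion of re-operations (primary outcome) within the control and intervention arms". Those inputs are 17% for control and 6.5% for intervention, with a two-sided likelihood ratio test, alpha 0.05 and 80% power.
- **Primary variable analyses.** The arms are compared by conventional logistic regression. No stage-weighted or combination statistic is mentioned.
- **Adjustment of significance levels and confidence intervals.** "Threshold for statistical significance is set at" P < 0.05 for the primary outcome. The only adjustment is for the secondary outcomes.
- **Composition of the coordinating center and trial steering committee {5d}.** The steering committee may implement changes to the protocol, and "All TMSC members will be lead- or sub investigators".

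**The concern.** The power calculation has two outcome inputs, one per arm. Its adequacy is to be re-checked on outcome data at a look where the arms are already being compared. One natural way to do this is to put the two observed rates into the formula and enlarge the trial if the answer exceeds 288. The final sample size then depends on the interim treatment difference, and an ordinary final test on all patients at 0.05 no longer has a known 5% error rate.

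Two further consequences would follow from such a rule. With about 50 patients per arm the observed difference is very imprecise, so the rule would often call for more patients even if the planning assumptions were right. And in an open trial whose primary event is a further operation, an extension decision that depends on the interim difference tells those who learn of it something about that difference.

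**Working it through.** **1. The planned size reproduces.** Inputs from Sample size {14}: 17%, 6.5%, two-sided 0.05, 80% power; mean rate 11.75%.

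- The likelihood ratio test needs noncentrality (1.960 + 0.842)² = 7.849.
- Per patient pair, the noncentrality is 2 × Σ [p ln(p/0.1175) + (1−p) ln((1−p)/0.8825)] over p = 0.17 and 0.065, which is 0.05487.
- n = 7.849 / 0.05487 = 143.06, so 144 per arm and 288 in total, as stated.

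The 288 is not in dispute. It does rest on both arm rates.

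**2. Type I error of the design with an extension.** The article gives no extension rule, so the rules and caps below are assumptions:

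- both arms have a true rate of 11.75%;
- the look is at 50 per arm, or at 37 per arm if fewer have reached 3 months;
- the trial stops if p < 0.001 at the look;
- otherwise it is re-sized to 80% power by the two-proportion formula, never below 144 per arm and never above the cap;
- the final pooled-variance test uses all patients at two-sided 0.05;
- each setting has 2 million simulated trials.

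| Re-sizing rule | Cap | 50 per arm at look | 37 per arm at look |
|---|---|---|---|
| None (0.001 look only) | 1x | 5.0% | 5.0% |
| Two observed arm rates | 1.5x | 5.5% | 5.4% |
| Two observed arm rates | 2x | 5.8% | 5.7% |
| Two observed arm rates | 3x | 6.1-6.2% | 5.9% |
| Pooled rate, planned odds ratio held | 1.5x to 3x | 5.1% | 5.0% |

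With both arms at 17%, 50 per arm and the observed-rate rule, the results are 5.6%, 5.8% and 6.2%.

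Normal-theory checks, with the look at 100/288 = 0.347 of the information:

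- The 0.001 look alone gives 5.05%, so it is not the problem.
- The worst possible extension rule gives 5.6%, 5.9% and 6.2% for caps of 1.5x, 2x and 3x.
- Re-sizing only when the interim effect favours embolization gives 5.3%, 5.4% and 5.6%.
- Extending only when conditional power is 50-80% gives 4.9-5.0% (caps 1.5x and 2x).

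**3. How often the observed-rate rule would extend if the plan is right.** With true rates of 17% and 6.5% and 50 per arm, the standard deviation of the observed difference is √[(0.17 × 0.83 + 0.065 × 0.935)/50] = √(0.2019/50) = 0.064. That is about 6.4 points against a planned difference of 10.5 points. Enumerating all outcomes, the rule asks for more than 144 per arm in 50% of trials and more than 288 per arm in 30%. In about 6% the interim difference is zero or reversed.

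**4. The planned odds ratio.** (0.065/0.935) / (0.17/0.83) = 0.0695/0.2048 = 0.34. With this held, any pooled rate yields a pair of arm rates and hence a size, with no knowledge of the observed difference.

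**The case against.** A reader might infer that the 5% level is definitely broken, or broken whenever the look is held. The text does not support that. It says preliminary data inform a decision; it does not say that observed arm rates drive it. A calculation built on 17% and 6.5% can be re-checked from the pooled rate against 11.75%, and comparing the groups for stopping does not make that comparison the input for re-sizing. Some permitted rules hold about 5%, as shown above.

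A reader might also infer that half of such trials would be extended, or that effect information would reach the steering committee. Both depend on the assumed arm-rate rule. The analysis is called independent, the DSMB consists of non-investigators, an independent data management committee performs the primary analysis, and nothing says the steering committee receives arm-level interim data.

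The inflation is modest, and the larger figures need a large extension: a cap of 3x means 864 patients. Finally, the article condenses a fuller protocol, and the analysis plan and DSMB charter are not shown. A detailed re-estimation rule could sit there, and its absence from the article is not a fault in itself.

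What remains is that the article itself fixes both halves: an extension informed by interim outcome data, and an ordinary final test at an unadjusted 0.05. Nothing in it confines the first so that the second is valid. Nor can the passage be read as concerning accrual speed alone. Inclusion rate has its own look at 30 participants (Dissemination plans {31a}), whereas the look at 100 names the power calculation.

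**Conclusion.** The point stands in a limited form: as worded, the plan permits an uncapped, effect-driven extension followed by an unadjusted test, so the 5% type I error is not guaranteed. Under plain re-sizing on the two observed arm rates, the error would be about 5.5-6.2% for caps of 1.5x to 3x with 50 per arm at the look, or 5.4-5.9% with 37 evaluable per arm. Those figures rest on an assumed rule, assumed caps and an assumed number evaluable, because the article states none of them. The roughly even chance of a needless extension, and the possible signal to investigators, carry the same condition. The size of the effect and the open reading make this a should-fix, not a must-fix.

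**What to change.** In Interim analyses {21b}, replace the open sentence with a rule along these lines: the sample size is re-assessed only from the reoperation proportion in both arms combined, holding the planned odds ratio (17% to 6.5%, about 0.34), never below 288 and up to a stated maximum; arm-specific rates are seen only by the DSMB and are not used for this decision. The final test at 0.05 can then stay as it is.

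If comparative data must be used, pre-specify a combination test with fixed stage weights as the primary test, together with the extension rule and maximum.

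Either version should be fixed before the look, since a rule chosen after comparative data have been seen cannot restore the error rate. The cost is protocol wording. The one downside of the pooled rule is that it cannot show that the treatment effect itself is smaller than planned.
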